**Methods/Design:**

The design of the study is a single layer multicentre superiority type randomised controlled trial of unilateral knee replacement patients. Blinding will not be possible as the surgical scars for each procedure differ.

We aim to recruit 500 patients from approximately 28 secondary care orthopaedic units from across the UK including district general and teaching hospitals. Participants will be randomised to either UKR or TKR. Randomisation will occur using a web-based randomisation system. The study is pragmatic in terms of implant selection for the knee replacement operation. Participants will be followed up for 5 years. The primary outcome is the Oxford Knee Score, which will be collected via questionnaires at 2 months, 1 year and then annually to 5 years. Secondary outcomes will include cost-effectiveness, patient satisfaction and complications data.

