### Primary outcome measure

The primary outcome measure for TOPKAT is the Oxford Knee Score (OKS). This is a patient-reported outcome questionnaire specifically designed and developed to assess function and pain after TKR surgery; it is a validated and effective measure of change over time [39]. Although patients will be contacted annually, the primary analysis will be at 5 years (and 10 years (subject to additional funding) post randomisation. An early analysis at 1 year is also planned.

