### Randomisation procedures

Randomisation will occur using a web-based randomisation service at the Centre for Healthcare Randomised Controlled Trials (CHaRT), Health Services Research Unit, University of Aberdeen.

The minimisation algorithm will incorporate gender, age and baseline OKS and ‘delivery unit’. A delivery unit is either an ‘equipoise surgeon’ or a pair of ‘expertise surgeons’ with complementary expertise (that is, one TKR-focused and one UKR-focused).

This factor is included to ensure balance is maintained for individual equipoise surgeons and more generally by centre. Participating surgeons will be discouraged from changing practice during the course of the trial. Within a centre there may be a mixture of delivery unit types. Local recruitment officers at each site will undertake the randomisation. The randomised treatment will be recorded in the patient’s hospital notes and study notes and the surgeon will be notified. If the allocated operation is not provided by the recruiting surgeon (for example, they are an ‘expertise surgeon’ who provide the other operation), an ‘internal referral’ to their delivery unit colleague will be initiated. A standard letter informing the admissions department/care-pathway coordinators will be sent. Local study staff will oversee this referral. Patients’ GPs will also be notified at this time.

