### Statistical analysis

Principle analyses will be based on an ‘intention to treat’ basis where participants will be analysed according to the allocated group using all available participant data. Statistical significance will be judged at the two-sided 5% level with corresponding 95% confidence interval presented. A short summary of the proposed analyses is given below. Further details of the planned statistical analyses are contained in the Statistical Analysis Plan, which will be finalised, prior to the unblinding of data.

Three sets of analyses are planned, based on the anticipated follow-up period. By 2 years, all patients are anticipated to have received surgery. Analyses are planned at 1 year post operation (3 years into the trial), at 5 years randomisation (7 years into the trial) and 10 years post randomisation (12 years into the trial).

Under the principal analysis of the primary outcome, the OKS score will be compared at each assessment point alone (multiple linear regression analysis adjusted for minimisation factors). The impact of adjusting for delivery unit will be explored using multilevel modelling. A stratified analysis (and associated interaction effect) will be performed to allow for a difference between expertise versus equipoise delivery of the treatments and the potential impact upon the comparison. Secondary analyses will explore the potential impact of missing data and alternative analytic approaches. In addition to the analyses planned once 5 and 10 year follow-up has matured, a complementary analysis will also compare the OKS over all assessments (the follow-up period) using multilevel modelling to allow for repeated measurements for participants. One secondary analysis, using an external comparative cohort, will also evaluate whether trial patients are representative, in terms of age, patient demographics and operative findings, of patients undergoing UKR and TKR in the general population.

Secondary outcomes will be analysed in a similar manner adjusting for minimisation factors where appropriate within a generalised linear models framework. Confidential interim analysis will be performed as requested by the Data Monitoring Committee.

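### The principal 5-year OKS regression, unless scores are imputed, ignores the earlier OKS of patients with no 5-year score; this costs a little precision and can bias the estimate if non-response differs by arm

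*Protocol article*

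**What the plan says.** All references are to the protocol article.

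- **Time point.** Under Primary outcome measure, "the primary analysis will be at 5 years", with 10 years to follow if funded.
- **Principal method.** Under Statistical analysis, "the OKS score will be compared at each assessment point alone (multiple linear regression analysis adjusted for minimisation factors". Randomisation procedures lists those factors as gender, age, baseline OKS and delivery unit. The effect of adjusting for delivery unit is to be explored separately in a multilevel model.
- **Repeated measures.** The same section then adds that "a complementary analysis will also compare the OKS over all assessments (the follow-up period) using multilevel modelling to allow for repeated measurements for participants".
- **Population.** "participants will be analysed according to the allocated group using all available participant data".
- **Missing data.** "Secondary analyses will explore the potential impact of missing data and alternative analytic approaches". No imputation is stated for the principal analysis.
- **Deferred detail.** "Further details of the planned statistical analyses are contained in the Statistical Analysis Plan", which is not available here.
- **Data at hand.** According to the abstract, the OKS is "collected via questionnaires at 2 months, 1 year and then annually to 5 years".

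**The concern.** A patient who completes the OKS for four years and misses the fifth has given a good deal of information about the missing score. A regression at 5 years alone, without imputation, discards it. For that analysis to be unbiased, the missing 5-year scores must be explained by treatment and the baseline covariates.

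Three features of this trial make that assumption worth questioning. Patients know which operation they had. The OKS comes by postal questionnaire, so response may depend on how the knee has been doing. The section on re-operation also anticipates that re-operation may be more frequent after UKR than after TKR, so the link between a poor result and non-response could differ by arm. The stake is the headline estimate, in a trial whose minimal clinically significant difference is 2.0 OKS points.

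**Working it through.** **Inputs from the article:** difference 2.0, SD 8.0, 250 per arm, two-sided 5%, 80% power (Primary outcome - OKS score). **Assumed, because the article gives no figures:** the fraction missing at 5 years (d), the correlation between an earlier post-operative OKS and the 5-year OKS (r), and the strength of the dependence of dropout on earlier OKS.

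**1. The plan's own figure.** n per arm = 2 × SD² × (1.960 + 0.842)² / difference² = 2 × 64 × 7.85 / 4 = 251.2, so 252 against 250 stated. With 250 per arm, the standard error is 8 × √(2/250) = 0.716, 2.0/0.716 = 2.795, and power is Φ(2.795 − 1.960) = 79.8%. The stated size is reproduced. Before covariate adjustment it leaves no margin for missing scores.

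**2. Precision.** If missingness depends only on observed scores, using the earlier OKS multiplies the variance by about 1 − d × r² relative to the single-time-point analysis. The effective number per arm is 250(1 − d)/(1 − d × r²). For d = 0.20 and r = 0.8 this is 200/0.872 = 229.4.

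| Missing at 5 years | Power, 5-year scores alone | Power using earlier OKS, r = 0.5 to 0.8 | Gain, points |
|---|---|---|---|
| 10% | 75.5% | 76.6% to 78.3% | 1.1 to 2.8 |
| 15% | 73.1% | 74.8% to 77.3% | 1.7 to 4.2 |
| 20% | 70.5% | 72.7% to 76.3% | 2.2 to 5.8 |

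The standard error falls by 1.3% to 6.6%. These figures leave out baseline adjustment. With it, at an assumed baseline correlation of 0.4, the SD becomes 8 × √(1 − 0.16) = 7.33, and the single-time-point analysis has 82.5% power at 10% missing and 77.9% at 20%.

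**3. Bias, hand check.** Suppose that in one arm the log-odds of dropout fall by β per point of year-4 OKS. To first order, the completers' 5-year mean in that arm is too high by r × β × d × SD². Take β = 0.06, an odds ratio of exp(0.06 × 8) = 1.6 per SD. At the mild end, 0.5 × 0.06 × 0.10 × 64 = 0.19. At the stronger end, 0.8 × 0.06 × 0.20 × 64 = 0.61.

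**4. Bias, simulation.** One million patients per arm, true difference 2.0, β = 0.06, d = 10% or 20%, r = 0.5 to 0.8, no baseline covariate:

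| Dependence of dropout on earlier OKS | 5-year scores alone | Using earlier OKS |
|---|---|---|
| Same in both arms | 1.94 to 2.00 | 1.98 to 2.01 |
| In one arm only | 2.17 to 2.55 | 1.98 to 2.00 |
| Opposite directions by arm | 2.39 to 3.20 | 2.00 to 2.02 |

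A separate simulation of 500 patients carried a baseline score (assumed baseline correlation 0.35, follow-up correlation 0.75, 15% to 18% missing, dropout from year 2 on the last OKS). With dependence in one arm only, the single-time-point bias was 0.35 at β = 0.06 and 0.72 at β = 0.10, and the longitudinal bias was at most 0.05 in size. With equal dependence in both arms, a true 2.0 was estimated as 1.96 and 1.87. The direction of any bias depends on which arm loses its poor scorers.

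**5. Dropout that depends on the unseen current score.** Under similar assumptions (16% missing, correlations 0.75 and 0.35), the bias was 0.5 to 0.9 for the single-time-point analysis and 0.1 to 0.3 for the longitudinal one. Using the earlier scores reduces this bias but does not remove it.

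**The case against.** **Deferred to the SAP.** The article is a summary, and the SAP may specify imputation. A reader might infer that patients without a 5-year OKS are excluded by rule. The article does not say so, and it speaks of all available data. What stands on the page is the ordering: regression at each point alone is principal, repeated measures complementary, missing data secondary. That is a stated choice and not a gap, but its consequence is conditional on no imputation.

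**The headline result is not shown to be biased.** A reader might infer that bias will enter the 5-year estimate. The article gives no dropout rate, mechanism or arm difference to support this. The sizeable figures arise only when dropout depends on OKS differently by arm.

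**Largely covered already.** Baseline-adjusted regression at a fixed time is a recognised primary analysis, and sensitivity analyses are planned. Both points are fair, and baseline adjustment recovers more power than the longitudinal model adds. The planned sensitivity analyses leave the headline estimate as it is, however.

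**The simulations favour the alternative.** Dropout was mostly generated from observed scores, the condition under which a longitudinal method works. The estimators were also regression-based stand-ins for a full multilevel model. Step 5 answers the first point in part: the advantage shrinks but remains. The second is a reason to specify the covariance carefully.

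**Not a simple exchange of two planned analyses.** This stands. A comparison over all assessments may estimate an average over follow-up and not the 5-year difference.

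**Conclusion.** The point holds as a worthwhile and inexpensive improvement. As written, and unless scores are imputed, the principal 5-year comparison makes no use of earlier OKS from patients who miss the 5-year questionnaire. The loss of precision is modest: about 1 to 6 points of power at an assumed 10% to 20% missing, with r between 0.5 and 0.8. Bias is conditional. It is roughly 0.2 to 0.7 points, or 10% to 35% of the 2.0-point target, if non-response depends on earlier OKS in one arm only. It is about 0.4 to 1.2 points if the dependence runs in opposite directions by arm. It is negligible, at most 0.13 points in the cases run, if dropout works alike in both. All these sizes rest on assumed missingness, correlations and dropout slopes.

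**What to change.** Define the principal estimate as the 5-year treatment contrast from a repeated-measures model of the post-operative OKS, with categorical time, treatment-by-time terms, baseline OKS, the other minimisation factors including delivery unit, and an unstructured covariance. Much the same can be had from the 5-year regression after multiple imputation that includes the earlier OKS. Report the single-time-point regression as a sensitivity analysis, and use the planned missing-data analyses to examine missingness that depends on unobserved scores. Do not simply promote the complementary model over all assessments: the 5-year contrast must be named.

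The cost is small. The scores are already collected, a multilevel model is already planned, and the article has the SAP finalised before unblinding. The downside is that a covariance or imputation model must be specified and checked. With six follow-up assessments to 5 years, an unstructured covariance has 6 × 7 / 2 = 21 parameters, which 500 patients should support.

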### Ethics

The study obtained approval from the National Research Ethics Service, Oxfordshire REC C in September 2009 (09/H0606/88).

### Trial status

Recruitment to the TOPKAT trial commenced in January 2010 and is ongoing at the time of manuscript submission. To date, 478 patients have been randomised (May, 2013). Recruitment was originally scheduled to end in December 2011. Early indications were that recruitment targets would not be met due to early delays with R&D approval process and time taken to incorporate the study procedures into the routine practice of participating sites. An extension to recruitment was discussed and recommended by the TMG and TSC which was agreed upon by the funders. The recruitment phase was extended to September, 2013.

## Abbreviations

AKSS: American knee society score; HAAS: High activity arthroplasty score; KAT: Knee arthroplasty trial; OKS: Oxford Knee Score; QALYs: Quality adjusted life years; TKR: Total knee replacement; UCLA: University of California Los Angeles; UKR: Unicompartment replacement.
